### 10.2 Pharmacology Study Design

10.2.1 Single sample for fluconazole at week 2

Plasma: At week 2, all participants in fluconazole induction cohorts will have whole blood collected for drug concentrations of fluconazole. For participants taking fluconazole once daily, the collection should take place 15-33 hours after the last dose of fluconazole and prior to the next dose of fluconazole. For participants taking fluconazole twice daily, the collection should take place 8-16 hrs after the last dose of fluconazole and prior to the next dose of fluconazole. For participants taking fluconazole more frequently than twice a day, sites should attempt to make the collection at least 4 hours after the most recent dose. The plasma PK sample should be obtained within 1 hour (ie, before or after) of the CSF collection described below.

CSF: A CSF sample must be obtained from all participants described in the paragraph above.

The date and time of the administration of all fluconazole doses for the previous 3 days and the day of the study visit as well as the date and time of plasma and CSF sampling will be recorded on the CRF.

- - 1. Single sample for fluconazole in participants taking RIF or EFV

Plasma: Whole blood will be collected for fluconazole concentrations and concentrations of the concomitant drug from all participants in the 1600 mg and 2000 mg daily fluconazole cohorts who are taking RIF and/or EFV (with no concomitant NVP) during the induction step. This collection should take place at least 2 weeks after the initiation of co-administration of fluconazole with the concomitant drug. For participants taking fluconazole once daily, the collection should take place 15-33 hours after the last dose of fluconazole and prior to the next dose of fluconazole. For participants taking fluconazole twice daily, the collection should take place 8-16 hrs after the last dose of fluconazole and prior to the next dose of fluconazole. For participants taking fluconazole more frequently than twice a day, sites should attempt to make the collection at least 4 hours after the most recent dose. The plasma sample should be obtained within 1 hour (i.e., before or after) of the CSF when CSF is collected as described below.

CSF: In addition, a CSF sample will be obtained for drug concentrations (if an LP is performed for other clinical or study purposes) from all participants taking part in this PK collection.

The following will be recorded on the CRF:

- date and time of all plasma and CSF samplings
- date and time of the administration of all fluconazole doses for the previous 3 days and the day of the study visit
- date and time of day (or actual or approximate time, if available) of all EFV doses for the previous 3 days and the day of the study visit (for participants taking EFV);
- date and time of day (or actual or approximate time, if available) for all RIF doses in the previous 3 days and the day of the study visit (for participants taking RIF daily);
- date and time of day (or actual or approximate, if available) for the last RIF dose including the day of the study visit (for participants taking RIF less frequently than daily).
  - 1. Single sample for fluconazole before and after dose reduction due to intolerability/toxicity

Plasma: All participants in the 1600 mg and 2000 mg daily fluconazole cohorts who require dose reduction of fluconazole due to intolerability/toxicity will have whole blood collected for fluconazole concentration at the time of the assessment of intolerability and prior to dose reduction. This sample can be obtained at any time during the induction step after the previous dose of fluconazole.

An additional sample will be collected at least 2 weeks after the dose reduction and while the participant is still taking the reduced dose. This sample may be obtained during a scheduled study visit. If the dose has resumed to full-dose, no sample should be taken for PK.

For participants taking fluconazole once daily, the collection should take place 15-33 hours after the last dose; for participants taking fluconazole, more frequently, the collection should take place 8-16 hrs after the last dose. For participants taking fluconazole more frequently than twice a day, sites should attempt to make the collection at least 4 hours after the most recent dose. The PK sample should be obtained within 1 hour (i.e., before or after) of the CSF sample described below is obtained.

CSF: In addition, a CSF sample will be obtained for drug concentrations from any participants involved in these PK collections for whom an LP is being performed for other clinical or study purposes.

For each sample, the date and time of the administration of all fluconazole doses for the previous 3 days and the date and time of blood and CSF sampling will be recorded on the CRF.

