2.1.1 Fluconazole

Fluconazole is a synthetic triazole antifungal agent. It is a highly selective inhibitor of fungal cytochrome P450-dependent sterol C-14 alpha-demethylation. The subsequent loss of normal sterols correlates with the accumulation of 14 alpha-methyl sterols in fungi and may be responsible for the fungistatic activity of fluconazole.

The pharmacology of fluconazole has been well studied only at doses of 50-400 mg per day. It is well absorbed orally (~ 90%), with peak plasma concentrations reached within 1-3 hours after dosing, and is not affected by food. Peak plasma concentrations at steady state on daily dosing are usually about twice those at trough. Fluconazole is minimally protein bound, widely distributed in body water with an apparent volume of 0.7 L/kg, and 80% is excreted unchanged in the urine with a half-life of 25-30 hours. About 11% is excreted in the urine as the glucuronide and N-oxide metabolites, which are both inactive and probably come from metabolism in the liver by cytochrome P450 3A4 enzymes. Renal insufficiency markedly prolongs the excretion of the drug.

Steady state is reached in plasma in 5-10 days on daily dosing, with steady state plasma concentrations of 4.6 and 9 mg/L after 200 and 400 mg doses, respectively. Cerebrospinal fluid (CSF) levels are 50-90% of those in serum [Foulds, 1988]. Over the range of 100–400 mg orally, the variation of fluconazole maximum plasma concentration (Cmax) and area under the concentration–time curve (AUC) are proportional to the administered dose. The elimination half-life and the time of Cmax also remain constant in this dosing range. This indicates the linearity of the pharmacokinetics (PK) of fluconazole for oral doses of 50-400 mg [Tett, 1995; data on file with Pfizer].

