5.1.3 Administration

Fluconazole

If needed to improve tolerance in the induction step, fluconazole may be administered with or without food and may be given in 2-4 approximately equally divided doses during a day.

Amphotericin B Deoxycholate

Amphotericin B deoxycholate should be administered intravenously under close clinical observation by medically trained personnel. Sites should refer to the current package insert. For additional information on administration and clinical management, sites may consult the Amphotericin B Deoxycholate Administration section in the A5225/HiFLAC MOPS.

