### 10.1 Pharmacology Objectives

10.1.1 Primary Objective

Compare concentrations of fluconazole in plasma and CSF at steady state for the doses tested in Stage 2. Samples from participants taking RIF or EFV at the week 2 PK collection will not be used in this comparison.

10.1.2 Secondary Objectives (for samples from participants who were not taking RIF or EFV at the week 2 PK collection)

10.1.2.1 Evaluate the relationship of fluconazole dose to fluconazole trough concentrations in plasma and CSF at steady state across the range of all induction doses studied.

10.1.2.2 Evaluate the relationship between fluconazole plasma and CSF concentrations in the doses tested in Stage 2 and change in cryptococcal concentration in CSF from baseline to week 2 and time to CSF sterility.

10.1.2.3 Evaluate the relationship between fluconazole plasma and CSF concentrations in the doses tested in Stage 2 and fluconazole toxicity or intolerance independent of dose as defined by Grade ≥ 3 toxicity, change in dose, or discontinuation of fluconazole.

10.1.2.4 Evaluate the relationship between fluconazole dose and plasma concentrations before and after dose reductions for toxicity or intolerance in the doses tested in Stage 2 (within-participant dose-to-plasma concentration comparisons).

10.1.2.5 Evaluate the relationship of fluconazole plasma and CSF concentrations with dose and demographic and physiological characteristics of participants including, but not limited to sex, weight, body mass index, and creatinine clearance.

10.1.2.6 Evaluate relationship of self-reported adherence to plasma and CSF trough fluconazole concentrations and to efficacy.

10.1.3 Secondary Objectives (for samples from participants who were taking RIF or EFV at the week 2 PK collection)

10.1.3.1 Evaluate plasma and CSF concentrations of fluconazole alone versus fluconazole when given concomitantly with RIF in the 1600 mg and 2000 mg daily doses, if sufficient numbers of samples are available.

10.1.3.2 Evaluate plasma and CSF concentrations of fluconazole alone at the 1600 mg and 2000 mg daily doses versus fluconazole given concomitantly with EFV, if sufficient numbers of samples are available.

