### 10.3 Primary and Secondary Data Analysis

The primary analysis will be a two-group t-test comparing the natural-log transformed plasma and CSF concentrations between all evaluable participants taking the doses tested in Stage 2 (i.e., participants taking these doses in Stages 1 and 2).

Secondary analyses will use various generalized linear models (e.g., standard regression for assessing impact of body mass index (BMI), race, gender, etc. on the trough concentrations; logistic regression for assessing impact of trough concentrations on toxicity, etc).

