### 10.4 Adequacy of Sample Size

We anticipate the availability of at least 1 plasma sample and at least 1 CSF specimen from approximately 40 Stage 1 and Stage 2 participants in each of the dose cohorts tested in Stage 2, allowing for sites unable to participate in this aspect of the study. We show power calculations allowing for 5 participants in each cohort that might be receiving RIF or EFV at the week 2 draw or who might not have sufficient CSF available for PK analysis. Assuming a 25% coefficient of variance (CV) within a dose level, samples from 35 participants would be adequate to detect a difference of approximately 20% of the lowest of the two means between the two dose concentrations with 90% power (alpha=0.05, two-sided).

For secondary analyses, with 70 observations available, we should be able to assess the impact of 3-4 factors in addition to dose level in a linear model.

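### The primary PK comparison ignores time since last dose although the week 2 sampling window is wide, which costs some precision that an adjustment using data already on the CRF could recover

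*Protocol*

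**What the plan says.** **Sampling (10.2.1).** Each participant in a fluconazole induction cohort gives one plasma and one CSF sample at week 2. On once-daily dosing, "the collection should take place 15-33 hours after the last dose of fluconazole and prior to the next dose of fluconazole". On twice-daily dosing the window is 8-16 h. On more frequent dosing, sites should try to wait at least 4 h. The times of all fluconazole doses over the previous three days and on the visit day go on the CRF, as do the sampling times.

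**Dosing frequency (5.1.3).** If tolerance requires it, the induction dose "may be given in 2-4 approximately equally divided doses during a day".

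**Objectives (10.1).** The primary objective compares plasma and CSF concentrations at steady state between the doses tested in Stage 2. Secondary objective 10.1.2.1 concerns "fluconazole trough concentrations in plasma and CSF at steady state across the range of all induction doses studied". Objective 10.1.2.3 relates concentration to toxicity or intolerance independently of dose.

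**Analysis (10.3).** "The primary analysis will be a two-group t-test comparing the natural-log transformed plasma and CSF concentrations between all evaluable participants" on the Stage 2 doses. No term, normalisation or restriction for sampling time or dosing frequency is named. BMI, race and gender are given as examples of factors for the secondary models.

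**Sample size (10.4).** "Assuming a 25% coefficient of variance (CV) within a dose level", the protocol states that "samples from 35 participants would be adequate" to detect a difference of about 20% of the lower mean, with 90% power at two-sided alpha 0.05.

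**Pharmacokinetics (2.1.1).** For fluconazole, "80% is excreted unchanged in the urine with a half-life of 25-30 hours". The section adds that the drug is well studied only at 50-400 mg a day.

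**The concern.** A level at 15 h, one at 33 h and one 4 h after a divided dose are different points on the concentration curve, even in the same person on the same daily dose. An unadjusted test treats them as interchangeable measures of exposure, so the differences enter as noise.

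If sampling time or divided dosing also differed between dose cohorts, part of the apparent dose effect would come from the schedule. Such a difference is plausible because splitting is allowed for tolerance. The same feature bears on objective 10.1.2.3: participants who tolerate the drug poorly are the ones whose dose may be split, and splitting raises the end-of-interval level at an unchanged daily dose. A link between concentration and intolerance could therefore arise from the schedule alone.

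**Working it through.** **Inputs from the protocol**
- 35 per dose, CV 25%, difference about 20%, two-sided alpha 0.05 (10.4).
- Sampling windows (10.2.1); 2-4 divided doses allowed (5.1.3).
- Half-life 25-30 h (2.1.1).
- Linear PK anticipated (10.5), so 1600 v 2000 mg gives an expected ratio of 2000/1600 = 1.25. Table 2 of the Schema lists these two doses as the fluconazole-alone cohorts of Stage 2.

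**Assumptions added here**
- One compartment, first-order elimination, absorption complete at sampling.
- CSF declines in parallel with plasma.
- The half-life holds at high dose.
- Draw times are spread evenly over the window.
- The 25% CV does not already contain timing variation.

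**Step 1: the plan's own figure.** With difference 0.20 and SD 0.25, n = 2 × (1.960 + 1.282)² × 0.25² / 0.20² = 33 per group. At 35 per group, power from the noncentral t is 91%. The statement in 10.4 is reproduced.

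**Step 2: the planned log scale.** SD = √ln(1 + 0.25²) = 0.246. At 35 per group, power is 86% for ln 1.20 = 0.182 and 96% for ln 1.25 = 0.223. The drop from 91% to 86% comes from the scale, not from sampling.

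**Step 3: effect of timing on one person's value.** k = ln 2 / half-life, which is 0.0277 per h (25 h) or 0.0231 per h (30 h).
- 15 v 24 h: exp(9k) = 1.28 or 1.23.
- 15 v 33 h: exp(18k) = 1.65 or 1.52.
- Twice daily, 8 v 16 h: exp(8k) = 1.25 or 1.20.

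As a check on the model, exp(24k) = 1.95 or 1.74. Section 2.1.1 puts the steady-state peak at about twice the trough.

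**Step 4: effect of dosing frequency.** For m equal doses at the same daily total, C(t) = (1/m) exp(-kt) / (1 - exp(-24k/m)). End-of-interval level relative to once daily at 24 h:

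| Doses a day | Half-life 25 h | Half-life 30 h |
|---|---|---|
| 2 | 1.20 | 1.16 |
| 3 | 1.27 | 1.22 |
| 4 | 1.31 | 1.25 |

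**Step 5: effect on power.** An even spread over w hours adds a timing SD of kw/√12 on the ln scale. Total SD = √(0.246² + timing SD²). Power at 35 per group (noncentral t):

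| Draws over | Timing SD | Total SD | Ratio 1.20 | Ratio 1.25 |
|---|---|---|---|---|
| No timing spread | 0 | 0.246 | 86% | 96% |
| 15-24 h | 0.060-0.072 | 0.253-0.257 | 83-84% | 95% |
| 15-33 h | 0.120-0.144 | 0.274-0.285 | 75-78% | 90-92% |

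**Step 6: bias, only under an assumed imbalance.** If divided dosing were 30 percentage points more common at one dose, the ratio of geometric means would shift by 5-6% for two doses a day (1.16^0.3 to 1.20^0.3) and by 7-8% for four (1.25^0.3 to 1.31^0.3). The 30 points are illustrative. The protocol gives no figure.

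**The case against.** A reader might infer that the sampling rules alone move the comparison by more than the 20% it is sized to detect. The documents do not support that. The 23-65% in step 3 is the spread of one person's value, whereas the 20% is a difference between group means. The rules are identical in all fluconazole cohorts, so with balanced timing there is no bias.

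A reader might also infer that the effect of 2000 mg is overstated because its participants split doses more often. The protocol says nothing about how often doses are split, or whether this differs by cohort.

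Other parts of the opposing case also stand:
- The sample must precede the next dose, so a once-daily draw after 24 h needs a delayed dose. Section 6.3.24 also reschedules PK visits after missed doses. The 15-24 h row is the more realistic one.
- The 25% CV may already include timing variation, and 10.4 does not say. If it does, step 5 counts that variation twice.
- Section 2.2 allows that clearance may saturate at high dose. A longer half-life would shrink every figure here.
- Power for the expected 1.25 ratio stays at about 90% even in the worst row.
- The secondary models are described by examples only, so they do not exclude timing or frequency.

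The deferral argument carries less weight. Section 9.2.3 sends pharmacology to separate analysis plans, but 10.3 itself names the primary test and leaves timing out of it.

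**Conclusion.** The point holds as a minor inefficiency. A wide, recorded and analysable source of variation is left out of the primary PK test. If the 25% CV excludes timing, the cost at 35 per group is about 2-3 percentage points of power for a ratio of 1.20 with draws over 15-24 h, and about 8-11 points in the extreme 15-33 h case. For the 1.25 ratio expected under linear PK, the cost is about 1 point, and at most about 6-7.

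Bias in the dose comparison is possible but not shown. It needs timing or divided dosing to differ between doses, and the size of any such difference is unknown. Confounding of the concentration-intolerance analysis by divided dosing does not need an imbalance between cohorts, so it deserves explicit handling there. All figures rest on a half-life established at 50-400 mg.

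**What to change.** In 10.3, replace the t-test with a linear model of ln concentration on dose cohort, adjusted for time since last dose. That time follows from the dose and sampling times that 10.2.1 already records.

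Add two sensitivity analyses: one that also includes dosing frequency, and one restricted to once-daily participants. Frequency stays out of the primary model because it is chosen after randomisation for tolerance and may partly result from high levels. Time since last dose overlaps with frequency, since divided dosing shortens it, so the sensitivity analyses are needed to interpret the primary estimate.

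Carry both variables into the concentration-response and concentration-toxicity models of 10.1.2, in particular 10.1.2.3. State in 10.4 whether the 25% CV includes variation in sampling time.

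The cost is one or two degrees of freedom of about 70, plus slightly more analysis work. Data collection, visits and dosing do not change.

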10.2.4 Single sample at time of Premature Treatment or Study Discontinuation

A single plasma sample for fluconazole levels will be collected at the time that Premature Treatment or Study Discontinuation evaluations are performed, except as noted in 6.2.4 for participants who are found to be HIV- and/or CM-negative.

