6.2.4 Premature Treatment or Study Discontinuation

Confirmatory HIV Test/Qualifying CSF culture

If **any of the following is true in the given time frame, then** the participant will be discontinued from study treatment, followed for up to 2 weeks, and then discontinued from the study**:**

- the confirmatory HIV test is negative
- the qualifying CSF culture is negative after 2 weeks of incubation
- **a confirmatory CSF antigen titer is negative by Day 5 AND no positive result from the qualifying CSF culture is obtained through Day 4**
- a study entry quantitative culture was required but not performed

In such cases, the participant will be treated as deemed appropriate by his/her primary physician. These participants should complete the evaluations in the Premature Treatment or Study Discontinuation column in the SoE at the time of treatment discontinuation and again approximately 2 weeks later, for study discontinuation; no fluconazole trough PK sample should be collected at these participants’ study discontinuation visit.

Premature Treatment Discontinuation

All participants who prematurely discontinue study treatment (see section 8.1) at any time during the study should complete the Premature Treatment or Study Discontinuation evaluations (per the SoE) within one week after treatment discontinuation. With the exception of participants randomized to ampho B who prematurely discontinue ampho B in Step 1 and who are eligible to register to Step 2, participants who prematurely discontinue study treatment will remain on the step they are on at the time of treatment discontinuation (without registering to subsequent steps) and will continue to be followed on study, off treatment per the SoE, except as noted in sections 6.3.22 and 6.3.24.

Premature Study Discontinuation

Participants who discontinue the study prematurely (see section 8.2) should complete the Premature Treatment or Study Discontinuation evaluations (per the SOE) at the time of study discontinuation.

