6.3.24 PK Sampling (see section 10.0)

Section 10.2 contains specific collection and reporting requirements and should be consulted prior to any collection.

PK samples will be collected only from participants who receive **study-provided** fluconazole during Step 1. Participants who prematurely discontinue study-provided fluconazole prior to exiting Step 1 will not undergo PK evaluations at subsequent visits.

NOTE: Under the following conditions, the PK collection should be rescheduled to occur within 1 week.

- If the participant has missed any doses of fluconazole within the previous 3 days or on the day of collection
- If a participant taking EFV has missed any doses of EFV within the previous 3 days
- If a participant taking RIF daily has missed any doses of RIF within the previous 3 days or on the day of collection
- If a participant taking RIF less frequently than daily has missed any doses of RIF within the previous week

With the exception of the week 2 sample, the CSF collection, when an LP is clinically indicated, should also be rescheduled, when the collection of PK samples is postponed.

If it is not possible to reschedule the CSF collection to coincide with a rescheduled PK visit, a single PK sample should be collected within 1 hour of the CSF sample collection at the originally scheduled visit. If it is not possible to reschedule the PK visit, a single sample should be collected at the originally scheduled PK visit.

In addition, a single plasma sample for fluconazole levels will be collected at the time that Premature Treatment or Study Discontinuation evaluations are performed from all participants who prematurely discontinue the study or prematurely discontinue study treatment, except as noted in 6.2.4 for participants who are found to be HIV- and/or CM-negative.

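### When toxicity stops fluconazole before week 2, the only related plasma level may be drawn up to a week later, too late to reflect exposure at the event

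*Protocol*

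**What the plan says.** - **Objective.** Protocol 10.1.2.3 relates plasma and CSF concentrations, in the doses taken into Stage 2, to "fluconazole toxicity or intolerance independent of dose as defined by Grade ≥ 3 toxicity, change in dose, or discontinuation of fluconazole". Section 10.3 gives logistic regression of toxicity on trough concentrations as the kind of model to be used.
- **Discontinuation sample.** Section 10.2.4: "A single plasma sample for fluconazole levels will be collected at the time that Premature Treatment or Study Discontinuation evaluations are performed". On timing, 6.2.4 says that participants who stop treatment early "should complete the Premature Treatment or Study Discontinuation evaluations (per the SoE) within one week after treatment discontinuation". Section 10.2.4 sets no hours-after-dose window and asks for no dose times. Sections 10.2.1 to 10.2.3 all ask for dose and sampling times.
- **No later sampling.** Section 6.3.24: "Participants who prematurely discontinue study-provided fluconazole prior to exiting Step 1 will not undergo PK evaluations at subsequent visits".
- **Dose reduction.** In the 1600 mg and 2000 mg cohorts, 10.2.3 takes a level "at the time of the assessment of intolerability and prior to dose reduction". It does not mention interruption or discontinuation.
- **Elimination.** Section 2.1.1: "80% is excreted unchanged in the urine with a half-life of 25-30 hours". The same section cautions: "The pharmacology of fluconazole has been well studied only at doses of 50-400 mg per day".

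**The concern.** Discontinuation is one of the toxicity definitions in 10.1.2.3, so each discontinued participant needs a concentration that reflects exposure when the toxicity arose. For dose reductions at 1600 and 2000 mg the protocol secures this by sampling before the change. It does not do so where the management sections go straight to holding or stopping drug, as 7.2, 7.3 and 7.5 do for certain grades of QTc, hepatic and rash toxicity.

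If such a participant stops before the week 2 visit, the level comes from a visit that may fall a week after the stop. The glossary defines a DLT as at least 3 consecutive days off an induction dose, begun before day 14, and the week 2 visit window is days 12-17. The gap therefore falls on DLT-type events. At stake is whether the pharmacology data can speak to exposure in those early cases.

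**Working it through.** **1. The protocol's own figures.** The protocol gives no figure for drug remaining at the discontinuation visit, so the half-life was checked against its other statements in 2.1.1.
- Peak-to-trough ratio over 24 h = 2^(24/t½): 1.95 at 25 h and 1.74 at 30 h, against a stated ratio of about two.
- Five half-lives: 5 × 25/24 = 5.2 days and 5 × 30/24 = 6.3 days, against steady state in 5-10 days.

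The half-life is consistent with both. The one power statement in the pharmacology plan (10.4: 35 per dose, CV 25%, 20% difference, two-sided 0.05) also reproduces: 0.20/0.25 × √(35/2) = 3.35, less 1.96 gives 1.39, so power is about 92% against the stated 90%. That calculation concerns the dose comparison and is not in question.

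**2. Who has no better level.**
- Stopped after week 2: a timed week 2 plasma and CSF level exists (10.2.1).
- Dose-reduced at 1600 or 2000 mg: a level before the reduction exists (10.2.3).
- Interrupted and restarted: the PK visit can be rescheduled (6.3.24).
- Stopped before week 2 with no earlier reduction: only the 10.2.4 sample. A progression visit would add one under 10.2.5, but that visit is not triggered by drug toxicity.

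**3. Longest compliant delay.** The week runs from discontinuation. Under 7.0, permanent discontinuation may follow an interruption of about 3 days. The delay since the last dose can therefore reach 72 + 168 = 240 h. The shortest is a same-day draw.

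**4. Drug remaining.** First-order elimination, fraction = 0.5^(t/t½), relative to the level just after the last dose:

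| Hours since last dose | t½ 25 h | t½ 30 h |
|---|---|---|
| 24 | 51% | 57% |
| 33 | 40% | 47% |
| 72 | 14% | 19% |
| 120 | 3.6% | 6.3% |
| 168 | 0.95% | 2.06% |
| 240 | 0.13% | 0.39% |

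Against a 24 h trough, the 168 h value is 0.5^(144/t½) = 1.8% to 3.6%. With slower elimination (assumed t½ 50-100 h; the protocol gives no value), 10-31% of the last-dose level remains at 168 h.

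**5. Can a late level be corrected back?** Scaling a 168 h level to a 24 h trough means multiplying by 2^(144/t½): 54 at 25 h, 28 at 30 h. The protocol's own half-life range leaves a factor of about two. A 12 h error in the time of the last dose adds a factor of 2^(12/t½) = 1.39 or 1.32.

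**6. Effect on the analysis (illustration only).** Assumptions: 80 participants, log-scale SD 0.25, true odds ratio 1.65 per SD, about 19% with toxicity, draw time uniform over 0-7 days since the last dose, half-life 25-30 h, 3,000 runs.

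| Toxic cases with only the late sample | Runs with toxic mean below non-toxic, if used as a trough | Toxic cases left, if dropped (from about 15.5) |
|---|---|---|
| 25% | 86% | 11.7 |
| 50% | 99% | 7.8 |
| 100% | 100% | 0 |

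With correct troughs, the sign is wrong in about 5% of runs. At 25% and 50%, dropping the cases left the mean difference about unchanged (0.12 on the log scale), because the simulation made reliance on the late sample unrelated to concentration. There the cost is lost cases.

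**The case against.** The strongest reply is that the protocol never says what the 10.2.4 sample is for. It is also taken at discontinuations unrelated to toxicity, and no passage puts it into the 10.1.2.3 model, which sits under a heading tied to the week 2 collection. Section 9.2.3 leaves pharmacology to separate analysis plans. This stands: a reader might infer that the protocol will use the sample as a trough, but it does not say so. Section 6.2.4 does call it a trough, though only when exempting participants found HIV- or CM-negative. An analysis plan can exclude a late sample; it cannot supply a level that was never drawn.

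Dosing history is partly captured elsewhere. Section 6.3.7 records interruptions of 2 or more days and permanent stops, and 6.3.28 asks about adherence over the previous 3 or 4 days. That usually gives the date of stopping. It does not give clock times, and a 3-4 day recall does not reach the last dose when the draw is a week later.

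Three stronger readings are tempting and not supported:
- That the worst toxicities in general will appear at the lowest exposure. The general rule in 7.1 is dose reduction, which triggers a sample at 1600 and 2000 mg, the fluconazole doses in the schema's Stage 2 table. Later stops have the week 2 level.
- That a one-day delay already swamps the 25% step from 1600 to 2000 mg. For once-daily dosing, 24 h is an ordinary trough, inside the 15-33 h window of 10.2.1.
- That the trial could not address exposure and toxicity at all. The objective also counts Grade 3 or higher toxicity and dose changes, many of which will have usable levels.

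**Conclusion.** The point holds for a defined subset: participants whose toxicity leads straight to discontinuation, or to an interruption that becomes permanent, before the week 2 PK visit and with no earlier dose-reduction sample. For them a compliant draw may hold about 1-2% of the level at the last dose, or 2-4% of a 24 h trough, and less if an interruption came first. That is the late end of the window. The figure rests on first-order elimination and a half-life studied at 50-400 mg/day; renal impairment or saturated clearance would leave more.

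Used as a trough, such samples push the exposure-toxicity relation downward and could reverse it. Omitted, the cases have no level. The protocol does not state how many participants are affected. For scale, the escalation rule in 9.3.1 implies 0-3 DLTs at a dose that is escalated and 4-9 at one declared the MTD, so the count may be small, but so is the total of toxicity cases. This is a cheap improvement to a secondary pharmacology objective within an exploratory plan. DLT counts, the MTD and efficacy analyses do not depend on it.

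**What to change.** 1. Extend 10.2.3, with matching notes in 6.3.24 and the schedule of events, so that the at-event plasma sample is also drawn when fluconazole toxicity leads to interruption or discontinuation. Draw it when the toxicity is assessed, without delaying any treatment decision.
2. In 10.2.4, record the date and time of the last dose, of doses in the previous 3 days and of the draw, using the fields already in place for 10.2.1 to 10.2.3.
3. State in 10.3 that a 10.2.4 sample taken outside the protocol's post-dose window (15-33 h for once-daily dosing, 8-16 h for twice-daily) does not count as a trough.

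The cost is an occasional unscheduled tube and a few existing data fields. Treatment and visit structure do not change.
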